### Study assessment

The study procedure through visits is schemed in figure 1.

**Figure 1 F1:**
[figure not shown]
Flowchart of study assessment; the method of follow-up and evaluation of participants in both intervention and control groups is given in this chart. Wk: Weeks, F/U: Follow-up, LDA: Low-dose aspirin, PE: Pre-eclampsia.

### Laboratory tests

At the same time, as the 11–14 wk ultrasound exam, a combined test will be requested to measure PAPP-A and beta-human chorionic gonadotropin using automated machines that provide reproducible results (the Cobas-E-411 analyzer, Ruche-Switzerland).

### Data collection

An electronic medical file was created for each patient to record demographic and obstetric information, physical examination results, laboratory tests, and imaging during each visit. In addition, all information related to unusual events such as obstetrical hospitalization, or aspirin side effects, and delivery information were recorded.

### Data collection methods

The participant's data will be entered into the information collection forms (Table II). Demographics, obstetrics characteristics, paraclinical results, delivery, neonate data, and perinatal outcomes will be entered into data collection forms. Finally, all the information will be entered in the electronic case report form which will be analyzed.

#### Consent for dissemination

Not enforceable- we have not rendered any identifying images or other personal, or clinical details of participants here.

#### Accessibility of data

This script constitutes the complete protocol. Following the completion of the study information used in this study will be obtained from the corresponding author upon rational request.

**Table 2 T2:** Data collection form

**Patient information**	
**Maternal demographic characteristics**	
**1**	Record of hypertension in a prior pregnancy
**2**	Chronic hypertension
**3**	Autoimmune disease: APs, SLE
**4**	Renal disease
**5**	Type 1 or 2 diabetes mellitus
**6**	Multiple fetuses
**7**	Nulliparity
**8**	History of PE in the mother or sister
**9**	BMI ≥ 30
**10**	Age ≥ 35
**11**	Low level socioeconomic
**12**	IVF
**13**	Obstetrical risk factors included SGA, PTL
**Paraclinical data**	
**14**	PE risk in first-trimester aneuploidy screening test
**15**	PAPP-A
**16**	Mean UtA-PI of the first trimester
**17**	Mean UtA-PI of the second trimester
**Delivery, neonate data, and outcomes**	
**18**	Gestational diabetes under insulin
**19**	Gestational diabetes without insulin
**20**	Weight gain during the 1 ${\;}^{\text{st}}$ trimester
**21**	Weight gain during the 2 ${\;}^{\text{nd}}$ trimester
**22**	Weight gain during the 3 ${\;}^{\text{rd}}$ trimester
**23**	Total weight gain
**24**	Gestational age at delivery
**25**	Birth weight
**26**	Postpartum hemorrhage
**27**	Drug-related side effects and adverse events
**28**	Placenta abruption
**29**	Early-onset PE
**30**	Late-onset PE
**31**	The requirement for NICU admission or mechanical ventilation
**32**	Neonatal respiratory distress syndrome
**33**	Hospitalization for maternal and fetal observation
**34**	Spontaneous PTL < 34 wk
**35**	Spontaneous PTL < 37 wk
**36**	IUFD or stillbirth > 20 wk
APs: Anti-phospholipid syndrome, SLE: Systemic lupus erythematosus, PE: Pre-eclampsia, BMI: Body mass index, IVF: In vitro fertilization, SGA: Small for gestational age, PTL: Preterm labor, PAPP-A: Pregnancy-associated plasma-A, UtA-PI: Uterine artery pulsetillity index, NICU: Neonatal intensive care unit, IUFD: Intrauterine fetal demise	

### Outcomes

#### Primary outcome

The primary outcome is determining the occurrence of early-onset (
<
 34 wk) and late-onset (
≥
 34 wk) PE. PE is described by the International Society for the study of hypertension in pregnancy (18); as systolic blood pressure 
≥
 140 mmHg and/or diastolic blood pressure 
≥
 90 mmHg on at least 2 times 4 hr apart developing after 20 wk of gestation in previously normotensive women, and there should be proteinuria 
≥
 300 mg in 24 hr, or urinary protein creatinine ratio 
≥
 30 mg/mmol midstream, or catheter urine specimens if no 24-hr collection is available, or 2 readings of at least ++ on dipstick analysis of midstream, or in the absence of proteinuria, new-onset hypertension with any of the following:

- Thrombocytopenia (platelet count 
<
 100000/µL)

- Renal insufficiency (serum creatinine 
>
 1.1 mg/dL)

- Impaired liver function as described by liver transaminase levels at least twice the normal concentration

- Pulmonary edema

- Persistent cerebral or visual symptoms

PE symptoms are measured clinically in every visit and paraclinical tests are requested if symptoms are present.

During each visit, clinically determined PE symptoms shall be measured and paraclinical tests must be performed where symptomatic signs are present.

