### Primary objective

To determine the effectiveness of early use of LDA in high-risk pregnancies in reducing the incidence of early and late-onset PE.

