### Sample size

The sample size estimation of the main RCT was based on data from the ASPRE trial (6). The results of this trial showed that preterm PE occurred in 1.6% of the intervention group as compared with 4.3% in the placebo group. We calculated that the enrollment of 1792 participants in a 1:1 ratio of distribution (896 participants in each group) would provide the trial with a power of 90% (alpha level of 5%). If we are allowed a 10% loss to follow-up, the sample size will reach 986 participants in each group. A total of 1972 eligible participants will be randomly selected to participate in the trial arms. Furthermore, we proposed a sample size of 200 high-risk pregnancies in the pilot study and quality control. By screening 1686 pregnant women who attended the Maternal-Fetal hospital Clinic, we achieved this sample size. From January 2023, after obtaining written conscious consent, the trial began with 100 participants in each group at a 1:1 ratio, randomly.

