### Monitoring

During the trial, some participants may be excluded from the study due to reasons such as abortion or IUFD below 20 wk of gestation or major fetal abnormalities or side effects of aspirin. In case of severe side effects and the need to discontinue the drug, the data will be placed in the data proportion of the discontinuation and will be removed from the final analysis. Since the trial is not blind for the researchers, they can access the results at any stage, due to the nature of the intervention.

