### Statistical analysis

For all primary analyses, the intervention group will be compared to the control group. Statistical analyses will be performed using STATA statistical software version 17.0 (STATA Corp, Texas, USA) and SPSS version 25 (SPSS, Inc., Chicago, IL, USA). Descriptive data will be reported as the mean 
±
 SD, median (IQR), or count (percent) as appropriate. The Shapiro-Wilk normality test will be applied to test the normality of the quantitative data. Continuous data will be compared between 2 groups using an independent sample *t* test or Mann-Whitney U test, and categorical data will be compared using the Chi-square test. Finally, to find the independent effect of aspirin treatment in high-risk participants a multiple logistic regression test will be used, in which the effect of aspirin treatment will be adjusted for the background variables of the participants that will differ between the 2 groups. The level of significance was 
<
 0.05. A complete set of descriptive statistics will be produced for all variables overall and by the treatment group. Graphical displays will be produced as appropriate.

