#### Secondary analysis

By using appropriate tests, the secondary outcomes will be compared between study groups. The p-value and 99% CI will be generated for the treatment results.

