## 3. Discussion

Trophoblastic invasion into the myometrium portion of the spiral arterioles during normal placentation is performed in a 2-stage process. It starts at 6–8 wk of gestation and culminates at 16–20 wk. During this process, the spiral arteries are replaced with wide nonmuscular channels insensitive to vasomotor control. Incomplete deep placentation has been associated with a spectrum of pregnancy complications including PE (19).

PE is caused by the inability of trophoblast cells to invade the spiral arteries of the myometrial layer. Lyall and colleagues found that vascular spasms and inefficient blood circulation inside the fetoplacental unit are caused by ineffective trophoblast invasion (20).

The incidence of disease may be halved by LDA consumption before 16 wk of gestation (21). In one systematic review study, aspirin reduces the risk of preterm PE only when initiated at 16 wk of gestation and taken at a daily dose of 100 mg, but not term PE (22). Meta-analysis recommended that aspirin use before 17 wk decreases the risk of PE in SGA neonates (23). The mechanism of aspirin remains obscure, but it could include recovery of the alteration of uterine spiral arteries (22, 23). The level of platelet activation in pregnant women with PE is significantly higher than that in pregnant women without PE. This is shown by a shortened activated partial thromboplastin time and a hypercoagulable state. Aspirin can help regulate the balance between thromboxane and prostacyclin, and can also inhibit platelet aggregation. This can prevent the formation of small blood clots, reduce damage to organs caused by blood clots, and help to prevent PE (4, 5, 24).

Other studies found LDA improves altered cytokine production and has positive effects on sFTL1 production (9, 10).

We designed an RCT to investigate whether the earlier administration of aspirin from the first stage of spiral arteries invasion in the process of the placentation could further reduce the incidence of PE. We also speculate that aspirin administration at the same time as the spiral arteries transformation may be more effective in the prevention of PE and other complications related to these vessel disorders. In addition, this trial was designed to compare the effectiveness of aspirin administration at this time versus administration after 11 wk to prevent early and late-onset PE.

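### The two-part primary outcome has no success rule, the 90% power is for an outcome the trial does not list, and outcome results are open throughout

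*Protocol article*

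**What the plan says.** - **Primary outcome.** "The primary outcome is determining the occurrence of early-onset" PE, before 34 weeks, together with late-onset PE, from 34 weeks. The Primary objective names both: "To determine the effectiveness of early use of LDA in high-risk pregnancies in reducing the incidence of early and late-onset PE". Table II records them as separate items (29 and 30) and has no item for any PE.
- **Level.** Statistical analysis speaks of primary analyses in the plural, "For all primary analyses, the intervention group will be compared to the control group", and gives one level: "The level of significance was" below 0.05. It states no order of testing, division of alpha or success rule.
- **Sample size.** The calculation uses a different outcome: "The results of this trial showed that preterm PE occurred in 1.6% of the intervention group", against 4.3% on placebo. It yields 896 per group for 90% power at 5%. Preterm PE is in neither the primary nor the secondary outcome list.
- **Access.** Monitoring says of the unblinded researchers that "they can access the results at any stage". No interim test, boundary or limit on outcome data is described.
- **Secondary outcomes.** "The p-value and 99% CI will be generated for the treatment results", beside the general 0.05 level.

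**The concern.** A trial with two primary components and one alpha needs a rule for what counts as success. Any PE, both components and either component are three different claims, with different error rates and different power. Here the choice is open.

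It could matter in practice. If earlier aspirin moved some cases from before to after 34 weeks, early-onset PE would fall and late-onset PE would rise, and the article gives no reading for that result. Late-onset PE also pools cases at 34 to 36 weeks with term PE, and the Discussion itself cites a systematic review in which aspirin lowered preterm PE "but not term PE".

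The outcome that justifies the sample size is not one the trial undertakes to test. A reader who takes 90% as the power for early-onset or late-onset PE has no basis for it. Open access to results means that the choice between claims could be made with data in view.

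**Working it through.** **1. The protocol's own figure.** Inputs from Sample size: p1 = 0.043, p2 = 0.016, alpha 5% (taken as two-sided), power 90%, ratio 1:1.

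n = [z(0.975)·√(2·p̄·q̄) + z(0.90)·√(p1q1 + p2q2)]² / (p1 − p2)², with p̄ = 0.0295

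= [1.960 × 0.2393 + 1.2816 × 0.2385]² / 0.027² = 0.6001 / 0.000729 = 823.2, that is 824.

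With the continuity correction, n/4 × [1 + √(1 + 4/(n × 0.027))]² = 895.8, that is **896**. The figure is reproduced exactly, for preterm PE tested once at two-sided 5%.

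**2. Type I error by success rule.** Early-onset and late-onset PE are mutually exclusive and, at low rates, nearly independent. The simulation used 896 per arm, no effect, and assumed rates of 1–2% (early) and 5–8% (late).

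| Success means | Calculation | Type I error |
|---|---|---|
| Either component at 0.05 | 1 − 0.95² | 9.75% (simulated 9.7–9.9%; bound 10%) |
| Both components at 0.05 | 0.05² if neither is affected | about 0.25%; at most 5% in general |
| Any PE at 0.05 | one test | 5% |
| Either component at 0.025 | 1 − 0.975² | 4.94% |

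**3. Power for a component.** The article gives no early-onset or late-onset rate, so the control early-onset rate is an assumption. Keep the protocol's ratio 0.016/0.043 = 0.372 and 896 per group, without continuity correction:

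power = Φ{[√896 × (p1 − p2) − 1.960·√(2·p̄·q̄)] / √(p1q1 + p2q2)}

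- Control 1%, intervention 0.37%: Φ[(0.1880 − 0.2288)/0.1166] = Φ(−0.35) = **36%**
- Control 2%, intervention 0.74%: Φ[(0.3759 − 0.3224)/0.1643] = Φ(0.33) = **63%**
- Control 3%, intervention 1.12%: Φ[(0.5639 − 0.3935)/0.2003] = Φ(0.85) = **80%**

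The same formula gives 92% for 4.3% vs 1.6%, so that is the like-for-like comparison. The ratio comes from aspirin against placebo, whereas both arms here receive aspirin. That also bears on power, and it is a reason to treat these figures as illustrations only.

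**4. Cost of splitting alpha.** At 0.025 (z = 2.2414), the protocol's preterm-PE rates and its continuity-corrected formula, 896 per group corresponds to 823.2 uncorrected:

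Φ[(√823.2 × 0.027 − 2.2414 × 0.2393)/0.2385] = Φ(1.00) = **84%**

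Restoring 90% needs 972.6 uncorrected, which is **1046** per group after correction. With the protocol's own 10% allowance that is 1046 × 1.1 = 1151 per group, 2302 in total, against 1972 planned.

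**5. Intervals and level.** A 99% interval corresponds to |z| > 2.576 and a 0.05 level to |z| > 1.960. A secondary result with p between 0.01 and 0.05 would therefore meet the 0.05 level while its 99% interval generally still included no effect.

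**The case against.** - **Separate testing is not stated.** The primary outcome is written in the singular, and the Objective and Discussion also speak of reducing PE as a whole. Under an any-PE or both-required rule the error does not exceed 5%. Alpha allocation is often left to an analysis plan, and one may exist. This stands: the 9.75% is conditional. But separate recording of the two components and plural primary analyses make separate testing a plausible reading. The choice of primary outcome also belongs in the protocol, and this article calls itself the complete one.
- **The endpoint mismatch does not raise type I error.** A reader might infer that it does. It leaves the error alone and affects only power.
- **Access is not repeated testing.** A reader might attach repeated-look figures, such as 8.3% for two looks or 14.1% for five at 0.05. The article plans no interim test and no early claim of success, fixes enrolment at 1972, and provides a blinded analyst. Those figures describe a procedure that it does not contain.
- **Wider secondary intervals inflate nothing.** Correct; this is a reporting inconsistency.
- **The late-onset argument is partly preference.** The cited review asks a different question from early versus later start, and a preterm outcome would likewise count a delay past 37 weeks as prevention. This stands, so no claim is made that late-onset PE is a wrong outcome. A success rule is needed whichever outcome is kept.
- **Changing the primary outcome mid-trial under open access is itself a risk.** This also stands, and it is why the second option under the fix is offered and why either change must be dated and declared.

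**Conclusion.** The point holds in three separate parts.

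1. The success rule is undefined. The family-wise type I error is about 9.75% if either component suffices, and at most 5% if both are required or the components are pooled. The article does not support the statement that the error does exceed 5%.
2. The stated 90% power is arithmetically right for preterm PE but does not apply to the stated primary outcome. Power for early-onset PE cannot be fixed from the article; the range of 36% to 80% rests on assumed control rates of 1% to 3% and on the borrowed rate ratio.
3. The access sentence leaves room for the claim to be chosen after seeing data. How much that would inflate the error cannot be computed from the document.

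The mismatch between 99% intervals and the 0.05 level is minor.

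**What to change.** Before any outcome is viewed by arm, take one of two routes:

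- **Single primary.** Name preterm PE, the outcome already used for the sample size, as the only primary, with early-onset, late-onset and any PE as secondaries in a stated order. The article does not define preterm PE; taken as PE with delivery before 37 weeks, it can be derived from Table II items 24, 29 and 30.
- **Keep the two components.** State whether success means any PE, both or either. If either suffices, split alpha or fix the order of testing. Restate the power for that outcome with explicit assumed rates. At 0.025 each and the protocol's preterm-PE rates, 896 per group gives about 84%.

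In either case:

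- Replace the access sentence in Monitoring with a rule that no outcome is tabulated by arm before database lock, except safety data.
- Match the secondary intervals to the level: 95% with 0.05, or 99% with 0.01.

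**Cost.** Protocol and registry wording, and no new data. Late-onset PE may lose primary status, or the stated power becomes less favourable. Because recruitment to the main trial began in October 2023, the change must be dated and declared as made without sight of outcomes by arm. Since the pilot data are to be analysed and published, the declaration should also say whether pilot results by arm had been seen.

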#### Inclusion criteria

I. No serious maternal illness or learning difficulties

II. Pregnancies at risk of PE conforming to the USPSTF (13), ACOG, and SMFM (14) guideline criteria:

If there are one or more of the following criteria (major criteria), participants are considered at high risk:

1) Prior pregnancy with PE particularly early-onset PE or with an adverse outcome

2) Chronic hypertension

3) Type 1 or 2 diabetes mellitus

4) Renal disease

5) Autoimmune disease (antiphospholipid syndrome, systemic lupus erythematosus)

6) Multifetal gestation

If there are 2 or more of the following criteria (moderate criteria), they are considered high-risk:

1) Nulliparity

2) Obesity (body mass index 
>
 30 kg/m^2^)

3) Age 
≥
 35 yr

4) Family history of PE in mother or sister

5) Obstetric risk factors (such as a history of low birth weight or SGA, and other adverse pregnancy outcomes, 
>
 10 yr pregnancy interval)

6) Low socioeconomic level

7) In vitro fertilization (IVF)

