#### Exclusion criteria

1) Hypersensitivity to nonsteroidal anti-inflammatory drug products

2) Asthma, rhinitis, and nasal polyps

3) Severe renal or severe hepatic impairment

4) History of gastrointestinal bleeding or active peptic ulcer disease

5) Vaginal bleeding or significant hematoma on ultrasound

6) Gestational age 
>
 16 wk

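### Women with chronic hypertension are eligible, but the primary outcome as defined cannot occur in them, because both of its routes require new hypertension

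*Protocol article*

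**What the plan says.** Inclusion criteria (protocol article, Materials and Methods) lists "2) Chronic hypertension" among six major criteria and sets the threshold at one: "If there are one or more of the following criteria (major criteria), participants are considered at high risk". None of the six exclusion criteria removes it; the nearest concerns severe renal or hepatic impairment. The data collection form (Table 2, item 2) records it at baseline.

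The section Primary outcome counts early-onset (before 34 wk) and late-onset (34 wk or later) pre-eclampsia and gives two routes to the diagnosis:

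- **With proteinuria:** raised blood pressure "on at least 2 times 4 hr apart developing after 20 wk of gestation in previously normotensive women", plus proteinuria.
- **Without proteinuria:** "in the absence of proteinuria, new-onset hypertension with any of the following", followed by five organ criteria (platelets, creatinine, transaminases, pulmonary oedema, cerebral or visual symptoms).

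The form has one field for early-onset and one for late-onset pre-eclampsia (items 29 and 30). The objectives, the outcome sections, the form and the statistical analysis section contain no definition of superimposed pre-eclampsia and no rule for women who were already hypertensive.

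**The concern.** The eligibility rule and the endpoint rule describe different populations. A woman who enters because of chronic hypertension is neither previously normotensive nor able to develop hypertension for the first time. Whatever new proteinuria, thrombocytopenia or pulmonary oedema she develops after 20 wk, the written definition does not score her as a case.

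Two outcomes are possible, and they are alternatives for any given case:

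- **Definition applied literally.** These women contribute to both denominators and to neither numerator. Event rates and the absolute risk difference shrink, and the primary objective, pre-eclampsia in high-risk pregnancies, is not addressed for a group classed as high risk on this criterion alone.
- **Definition applied loosely.** Superimposed disease is entered under items 29 and 30 by a criterion nobody has written down, in a trial whose Blinding section says neither participants nor researchers are blinded.

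This is not detail left to a fuller document. The article states an explicit definition that conflicts with its own entry criteria, and under Accessibility of data it calls itself the complete protocol.

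**Working it through.** **Step 1: the text.** Entry: chronic hypertension is sufficient. Exclusion: it is not removed. Route 1: requires previous normotension. Route 2: requires new onset. A woman with chronic hypertension therefore meets neither route. This conclusion needs no figures.

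**Step 2: reproduce the plan's sample size.** Inputs from Sample size: 4.3% versus 1.6%, power 90%, alpha 5% (taken as two-sided), 1:1. With mean rate 0.0295 and d = 0.027:

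m = [1.960·√(2·0.0295·0.9705) + 1.282·√(0.043·0.957 + 0.016·0.984)]² / 0.027² = 823.2

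Continuity-corrected n = (m/4)·[1 + √(1 + 4/(m·d))]² = 895.8, so 896 per group. This matches the plan. Corrected power at 896 per group is 90.0%.

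**Step 3: power if these women cannot have events.** The documents give neither the share f of women with chronic hypertension nor their risk r relative to the others, so both are assumed. If the relative effect of aspirin timing is the same in both groups of women, the share of cases that cannot be counted is

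s = f·r / (f·r + 1 − f)

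Each rate is multiplied by (1 − s). For f = 10%, r = 3: s = 0.30/1.20 = 25%, giving 3.225% versus 1.2%. Power at 896 per group is found by inverting the corrected formula, with m = (n − 1/d)²/n.

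| Assumed share f | Assumed relative risk r | Cases not countable | Power (corrected) |
|---|---|---|---|
| 5% | 1 | 5% | 88.3% |
| 5% | 2 | 10% | 86.5% |
| 10% | 2 | 18% | 82.5% |
| 10% | 3 | 25% | 78.7% |
| 15% | 3 | 35% | 72.1% |
| 20% | 3 | 43% | 65.3% |

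The absolute risk difference shrinks by the percentage in the third column.

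**Step 4: would counting them restore power?** Take f = 10%, r = 3 and an overall control rate of 4.3%. Control risk in the other women is 0.043/1.20 = 3.58%, and in women with chronic hypertension 10.75%. The planned risk ratio is 1.6/4.3 = 0.372. The intervention rate is 0.9·0.0358·0.372 = 1.20% from the other women, plus 0.1·0.1075 = 1.075% times the risk ratio in women with chronic hypertension.

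| Effect in women with chronic hypertension | Intervention rate | Power when counted |
|---|---|---|
| Equal (0.372) | 1.60% | 90% |
| Half on the log scale (0.610) | 1.86% | 82% |
| None (1.0) | 2.28% | 62% |

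Leaving them uncounted gives 79% in the same scenario. So even the direction of the power change depends on an effect that the documents do not give.

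**The case against.** The strongest reply accepts the textual gap and disputes its consequences.

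- **No directional bias.** Allocation is randomised and the definition is the same in both arms, so a literal reading narrows the endpoint to new-onset disease and costs events. This stands.
- **The power figures are fragile.** The share and the risk are assumed, an equal relative effect is assumed, and the 4.3% and 1.6% are preterm pre-eclampsia rates for aspirin against placebo. This trial compares earlier with later aspirin on early- and late-onset disease. This stands: the figures illustrate the plan's own calculation, not the trial's real power.
- **Blinding.** Trial design calls the trial assessor-blind and the Blinding section promises a blind analyzer. That offers some protection, but blinding an analyst cannot supply a missing case definition, and the section says researchers know the allocation.
- **Changing the endpoint now carries its own risk.** Recruitment to the main trial has begun, and Monitoring says researchers can see results at any stage. This stands and shapes the fix.

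A reader might infer three stronger claims. One is that superimposed cases will both be missed and be ticked ad hoc; these are alternatives, and the documents do not say which will happen. Another is that these women carry the highest risk of all those enrolled; the protocol lists six major criteria without ranking them. The third is that the trial is underpowered by a known amount; the documents contain no figure from which to derive one.

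**Conclusion.** The contradiction is real and does not depend on prevalence: the stated rule, followed exactly, can never score an enrolled group of women as primary events. The consequence is lost events and an unanswered part of the primary objective or, if superimposed disease is recorded anyway, case counts that rest on an unwritten rule. Neither randomisation nor a blinded analyst repairs the definition.

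The size cannot be fixed from the documents. With shares of 5–20%, 1–3 times the risk and an equal relative effect, power on the plan's own calculation lies between about 88% and 65%, against a stated 90%. If timing has less effect in women with chronic hypertension, counting them need not restore it. The case for correction therefore rests on a coherent endpoint, not on a power figure.

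**What to change.** Reconcile Inclusion criteria with Primary outcome. Add a research-endpoint criterion for superimposed pre-eclampsia in women with chronic hypertension, built from the proteinuria and organ criteria already listed under Primary outcome, first appearing after 20 wk, and split at the same 34 wk boundary.

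Date the amendment and settle it without reference to outcome data by arm. Have someone unaware of allocation apply it identically in both arms. Report the primary result with and without women with chronic hypertension.

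The drafting cost is small; the application cost is not. Classification of superimposed disease is noisier. For women already enrolled, baseline status may not be recoverable: the first-visit measurements named under Intervention are vital signs, weight and height, the form has no baseline proteinuria or organ-function field, and Primary outcome calls for tests only when symptoms are present. Cases that cannot be classified should be reported as such, by arm. The rule concerns outcome classification only and changes nothing in clinical management.

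### Chronic hypertension alone qualifies a woman for the trial, but the primary outcome definition can only be met by women who were previously normotensive

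*Protocol article*

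**What the plan says.** **Eligibility.** Under Inclusion criteria, one major criterion is enough: "major criteria), participants are considered at high risk". The major list includes "2) Chronic hypertension" and "4) Renal disease". The Exclusion criteria do not remove women with chronic hypertension. They do remove severe renal impairment. Chronic hypertension and renal disease are both items on the data collection form (Table 2).

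**Primary outcome.** "The primary outcome is determining the occurrence of early-onset" disease (before 34 weeks) and late-onset disease (34 weeks or later). Pre-eclampsia is then written out with thresholds, by two routes:

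- raised blood pressure "developing after 20 wk of gestation in previously normotensive women", together with proteinuria;
- "in the absence of proteinuria, new-onset hypertension with any of the following", followed by a list of organ findings that includes serum creatinine above 1.1 mg/dL.

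The article gives no definition of superimposed pre-eclampsia, no other outcome rule for women who enter with hypertension, and no statement that they leave the primary analysis.

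**The concern.** Both routes to the event need hypertension that was absent before. A woman enrolled because of chronic hypertension fails that condition on the day she is randomised. There are then two ways to run the trial, and neither is satisfactory.

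- **Literal application.** These women count in the denominator but cannot contribute an event. The overall event rate and the absolute difference between arms shrink, and the primary objective, which concerns high-risk pregnancies as a whole, is not addressed for this group.
- **Loose application.** Staff record superimposed disease as pre-eclampsia by judgement. The Blinding section says that neither participants nor researchers are blinded, and the Primary outcome section says that paraclinical tests are requested when symptoms are present. Unblinded staff would therefore produce much of the evidence, and the blinded assessor would have no written rule to apply to it.

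A secondary and narrower point runs in the opposite direction. The definition does not require proteinuria, or creatinine above 1.1 mg/dL, to be new. In an eligible woman whose renal disease already meets one of these, new hypertension alone would complete the definition.

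**Working it through.** **Step 1. The text, side by side**

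| Element | What the article requires | Woman enrolled on chronic hypertension |
|---|---|---|
| Entry | One major criterion | Eligible; not excluded |
| Route 1 | Previously normotensive, raised pressure after 20 weeks, proteinuria | Cannot be met |
| Route 2 | New-onset hypertension plus organ finding | Cannot be met |
| Separate rule or removal from the analysis | None stated | Remains in the denominator as a non-event |

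**Step 2. Reproduce the plan's sample size**

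Inputs from the Sample size section: "preterm PE occurred in 1.6% of the intervention group as compared with 4.3% in the placebo group", 90% power, 5% alpha, 1:1 allocation, 896 per group. The article does not state sidedness; two-sided reproduces the figure.

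With p1 = 0.016, p2 = 0.043, d = 0.027 and mean rate 0.0295:

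- n0 = [1.960·√(2·0.0295·0.9705) + 1.282·√(0.016·0.984 + 0.043·0.957)]² / 0.027² = (0.469 + 0.306)² / 0.000729, which rounds up to 824 when computed without intermediate rounding.
- With continuity correction, n = (n0/4)·[1 + √(1 + 4/(n0·d))]² = 896, an exact match.
- Power at 896 without the correction: Φ[(√896·0.027 − 0.469)/0.2385] = Φ(1.42) = 92.2%.

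The stated 896 is sound on its own inputs. The problem is in the outcome definition.

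**Step 3. Illustrate the dilution**

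Let f be the share of events that arise in women with chronic hypertension and so cannot be counted. The article gives no value, so f is an assumption, taken as equal in both arms. Each rate is multiplied by (1 − f). Power is without continuity correction at 896 per group; the required n is with it.

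| f | Rates | Difference (points) | Power at 896 per group | n per group for 90% power |
|---|---|---|---|---|
| 0 | 1.60% v 4.30% | 2.70 | 92.2% | 896 |
| 5% | 1.52% v 4.09% | 2.57 | 90.9% | 945 |
| 10% | 1.44% v 3.87% | 2.43 | 89.3% | 999 |
| 20% | 1.28% v 3.44% | 2.16 | 85.4% | 1127 |
| 30% | 1.12% v 3.01% | 1.89 | 80.4% | 1292 |

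The ratio of the two rates stays at 0.016/0.043 = 0.37 in every row. Equal proportional loss costs events and absolute difference; it does not distort the relative effect.

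**Limit of this step.** The rates are for preterm pre-eclampsia under aspirin versus placebo. This trial counts early- and late-onset disease, and both arms receive aspirin. The table shows how sensitive power is to f; it does not forecast this trial.

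**The case against.** **An article condenses, and a fuller document may settle this.** That would answer an omission. Here the definition is written out in full and expressly restricted, and the article describes itself as the complete protocol. The cited society definition may treat superimposed disease separately, but that source is not at hand and the article's text does not carry such a rule over. The objection does not remove the conflict.

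**The practice may be sensible.** The data form has early- and late-onset pre-eclampsia as items, outcomes come from patients and maternity records, and a blinded analyser is promised. So it is not established that the count in women with chronic hypertension will in fact be zero. This stands: the zero follows only from literal application. The other possibility is classification without a written rule.

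**Randomisation balances these women.** This also stands. Literal application dilutes and narrows the result; it does not itself bias one arm against the other. A reader might infer bias between arms, but that would need informal classification that differs by arm, which the documents make possible and do not show.

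**The size is unknown.** A reader might take 896 × (0.016 + 0.043) = 52.9 as the expected events and subtract a share for chronic hypertension. The documents do not support such a count: the rates belong to a different outcome and a placebo comparison, and the article gives neither the prevalence of chronic hypertension nor the added risk.

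**The renal point is narrower than it looks.** Severe renal impairment is excluded, which removes the worst pre-existing creatinine values. Milder renal disease and pre-existing proteinuria remain eligible. No figure can be put on any over-counting.

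**Conclusion.** The primary outcome is wrong as written for part of the enrolled population. The Inclusion criteria and the Primary outcome section contradict each other: a criterion that alone qualifies a woman also makes the event unreachable for her. This rests on the text and needs no outside source or assumption.

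Its effect on power rests on an assumed share of events. If 10% to 30% of events were lost equally in both arms, power at 896 per group would fall from about 92% to between 89% and 80% on the plan's preterm rates. A loss of 5% would leave it just above 90%. Any larger claim, such as a specific number of lost events or a demonstrated difference in ascertainment between arms, goes beyond the documents. The missing newness condition for proteinuria and creatinine is a real but secondary gap, limited to renal disease short of severe impairment.

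**What to change.** Reconcile the Inclusion criteria with the Primary outcome section before outcomes are analysed:

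1. Prespecify how the primary outcome is determined in women with pre-existing hypertension, or state how these women enter the primary analysis.
2. Do the same for women with known renal disease or pre-existing proteinuria, saying whether findings present at entry can count.
3. Have the blinded assessor apply that rule to all participants in both arms.
4. Report the primary result separately for women with and without chronic hypertension.

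**Cost.** The text is short, and item 4 needs no new data because chronic hypertension is already on the form. The amendment is still a change to the primary outcome after main recruitment began in October 2023, in a trial whose researchers can see results at any stage, so it should be dated and justified. A rule based on change from entry is limited to the baseline data in the records. Blood pressure is taken at the first visit, but baseline proteinuria and creatinine are not listed on the form and may be unavailable for women already enrolled.
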